### Outcomes

The primary endpoint of the trial is HbA_1c_. There are multiple secondary endpoints including systolic and diastolic blood pressure, random cholesterol, HDL cholesterol, ApoA1 and ApoB apolipoproteins, CVD risk score as assessed by the UKPDS risk engine (version 2) [42] and additionally in London only, a measurement of arterial stiffness assessed by pulse wave velocity. Further secondary endpoints include anthropometry (waist circumference and body mass index) and serum concentrations of C-reactive protein (measured using a high sensitivity assay), fructosamine, and parathyroid hormone. Other endpoints include the safety of oral vitamin D without a pre-assessment of vitamin D status, the proportion of participants with a serum 25(OH)D in categories of <25, 25 to <50, 50 to <75, 75 to <150 and greater than or equal to 150 nmol/L measured by an LC-MS/MS (liquid chromatography–tandem mass spectrometry) assay, and the feasibility and acceptability of the intervention. The trial also assesses functional status (SF-8), health utility (EQ-5D) and total body pain (BPI).

### Intervention

In this trial the dose of vitamin D being used is 100,000 IU (equivalent to 2.5 mg) per month administered as four oral doses over consecutive months. The two investigational medicinal products (IMP) include cholecalciferol (prepared as Vigantol oil containing 20,000 IU vitamin D_3_ per ml in Miglyol vehicle oil), or ergocalciferol (prepared as Sterogyl containing 20,000 IU vitamin D_2_ per ml in ethanol). In the active intervention groups this represents a daily dose equivalent of ~3,300 IU. The placebo is Miglyol 812 oil with esters of coconut and palm-derived oils.

We chose the oral route of administration as this is the most commonly used in clinical practice, and it results in less inter-individual variability in achieved serum 25(OH)D concentrations compared to the intramuscular route [43]. It is also the route used by other investigators in studies which show safety of the dosage regimen used in this trial [44,45].

#### Investigational medicinal products

Vigantol oil (cholecalciferol) is manufactured by Merck Serono GmbH in the Federal Republic of Germany at a licensed site under GMP (Good Manufacturing Practices, WHO) conditions. Sterogyl (ergocalciferol) is manufactured by DB Pharma in France at a licensed site, also under GMP conditions. The placebo (‘Miglyol oil’), which is also the vehicle for vitamin D_3_ in Vigantol oil does not contain any pharmacologically active ingredient. The investigational agents are repackaged into randomisation packs by a commercial laboratory (Nova Laboratories).

### Safety

The vitamin D investigational medicinal products used in this trial have undergone safety and quality checks, and are prescribed by a registered medical practitioner in both study centres. We wanted to use an adequate dose of vitamin D and after careful consideration opted for a dose of 100,000 IU per month, in order to increase the likelihood of generating a significant difference in vitamin D status between the treatment and placebo groups. There have been several trials in which high doses of vitamin D were administered without any adverse events. In an Indian randomised controlled trial, supplementation in men with three doses of 120,000 IU of vitamin D at fortnightly intervals was not associated with any adverse events in general or specifically relating to hypercalcaemia [36]. In a Canadian trial, 4000 IU of vitamin D_3_ daily for 2–5 months in healthy adults did not result in any adverse effects [46]. Two clinical studies of 10,000 IU/day have demonstrated an elevation of serum 25(OH)D concentrations to the high end of normal concentrations without inducing toxicity in healthy volunteers [44,45]. The recent IOM (Institute of Medicine) aforementioned review revised the safe dose of vitamin D upwards from 2000 IU/day to 4000 IU/d, which the dose we are supplementing falls well within [21]. Side effects of vitamin D supplementation are rare and include gastrointestinal symptoms (such as nausea, constipation, or diarrhoea), hypercalcaemia, hypercalcuria and associated kidney stones. To minimise risk of hypercalcaemia and hypercalcuria amongst predisposed individuals, we exclude individuals with known sarcoidosis, malignancies and tuberculosis. As a safety precaution, three measures are recorded for all recruited participants at all trial visits: a point of care ionised calcium test, a laboratory serum corrected calcium test and a laboratory urinary calcium to creatinine ratio test. Trial participants who have high point of care ionised calcium (>1.3 mmol/L) or urine calcium:creatinine ratio (molar ratio >1) or serum corrected calcium > 2.65) are excluded from further doses of the IMP, but continue to be followed up. Additionally, provision has been made for the recording of adverse events or reactions.

### Recruitment

#### London site

Electronic searches of lists of patients in GP practices in East London are done by the practice staff to identify suitable participants. The Cambridge Risk Score (CRS) [38-41] is used to identify participants who are at high risk for T2D. In addition, a previous record of the presence of impaired glucose tolerance, impaired fasting glucose or non-diabetic hyperglycaemia assessed by HbA_1c_ is used to identify potential eligible participants. Practice staff extract information from the medical records on the following variables which comprise the Cambridge Risk Score: age, sex, smoking status, family history of diabetes, body mass index and whether the patient is prescribed anti-hypertensive or steroid medication. In addition, they extract information on ethnicity. Once identified, and after applying exclusion criteria that can be accessed from medical records, potential participants receive a letter inviting them to participate in the trial, a reply slip, a patient information sheet and a flyer with contact information. Potential participants who reply expressing an interest are telephoned by a member of the study team to provide further information as required and to arrange an appointment to attend a research centre.

### Cambridge site

In Cambridge, participants are recruited from the Fenland study, an on-going population-based observational study investigating the influence of lifestyle and genetic factors on the development of diabetes, obesity, and other metabolic disorders [47]. Residents of Cambridgeshire, in the east of England, born between 1950 and 1975 are potentially eligible to participate in the Fenland Study and are excluded by their general practitioner if they have been diagnosed with diabetes or a terminal illness with a prognosis of less than one year, have a psychotic illness, are pregnant or lactating, or if they are unable to walk unaided. Approximately 28% of those registered with participating general practices in the Cambridgeshire Primary Care Trust have enrolled in the Fenland Study (more than 8,000 participants). Fenland study participants are eligible for this trial if they had agreed to be contacted again to gauge interest in involvement in future studies and do not meet the trial exclusion criteria. Potential participants are mailed an invitation letter for the trial, an information sheet and a flyer with contact information. Those interested in taking part are asked to complete the response form and to return it in an enclosed freepost reply envelope. In the event of non-response, a second mailing is sent approximately four weeks after the first. Responders are excluded from the trial if they have been diagnosed with diabetes or are actively participating in another trial, or if any of the trial exclusion criteria apply. For eligible participants, telephone contact is made and any queries are addressed before setting an invitation date for the baseline visit. In Cambridge, HbA_1c_ is primarily used as the eligibility criterion for identifying increased risk of diabetes.

### Randomisation and blinding

Randomisation into three groups (cholecalciferol (D_3_), ergocalciferol (D_2_), or placebo) follows stratification of participants on the basis of age (two groups 30–50 and 51–75 years) and sex (male and female) into four groups, with a block size of 6 within each group.

In this double-blind trial, neither the participant, the investigators, nor the laboratory staff know whether participants have been allocated to vitamin D_2_, D_3_ or placebo during the course of the study. Since the IMPs are oil based or ethanol based products, in order not to compromise allocation concealment, the trial drug is administered by a person other than the investigator. The participants are also asked not to let the investigator know about any physical characteristics (including taste and feel) of the product that they have consumed.

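### Participant blinding is claimed for all three arms but secured only for D3 versus placebo, because D2 is given in ethanol and the only placebo is an oil

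*Protocol article*

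**What the plan says.** Under Randomisation and blinding, the protocol article calls the trial double-blind and states that "neither the participant, the investigators, nor the laboratory staff know whether participants have been allocated to vitamin D_2_, D_3_ or placebo" while the study runs.

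Under Intervention it gives the formulations:
- D3: "cholecalciferol (prepared as Vigantol oil containing 20,000 IU vitamin D_3_ per ml in Miglyol vehicle oil".
- D2: "ergocalciferol (prepared as Sterogyl containing 20,000 IU vitamin D_2_ per ml in ethanol".
- Placebo: "The placebo is Miglyol 812 oil with esters of coconut and palm-derived oils".

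Investigational medicinal products confirms that the placebo oil is the one "which is also the vehicle for vitamin D_3_ in Vigantol oil".

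The difference in vehicle is acknowledged under Randomisation and blinding: "Since the IMPs are oil based or ethanol based products, in order not to compromise allocation concealment". Two measures follow. Someone other than the investigator gives the product, and participants are asked to keep its physical characteristics, taste and feel among them, from the investigator. The same section sets four age-by-sex strata, "with a block size of 6 within each group".

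**The concern.** The statement about participants covers all three arms, yet one arm takes an ethanol solution and the other two take oil. A participant who notices alcohol and links it to D2 can infer both the arm and that the product is active. Both safeguards control what reaches the investigator; neither changes what the participant tastes.

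What is at stake is whether the two comparisons with placebo can be read alike. Both are presented as double-blind. D3 versus placebo has a matched vehicle and D2 versus placebo does not. Expectation could then shift self-reported outcomes in the D2 comparisons only. For tolerability, any effect of the ethanol vehicle itself would also be mixed with the effect of D2.

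**Working it through.** **1. The plan's own figure.** Sample size rounds 339 up to fit the block size. 339 / 6 = 56.5, so the next whole number of blocks is 57, and 57 × 6 = 342. The stated target reproduces.

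**2. Volume and number exposed.** A dose is 100,000 IU and both active products are stated at 20,000 IU per ml (Intervention). Taken as supplied, 100,000 / 20,000 = 5 ml per dose. With the equal groups implied by Sample size, 342 / 3 = 114 participants are in the D2 arm.

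**3. Vehicle match by contrast.**

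| Contrast | Vehicles | Role in the analysis | Participant blinding |
|---|---|---|---|
| D3 vs placebo | oil / oil | primary comparison | secured by matched vehicle |
| D2 vs placebo | ethanol / oil | primary comparison | not secured |
| D2 vs D3 | ethanol / oil | exploratory | not secured |

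A participant who recognises oil learns at most that the product is not D2. D3 and placebo remain equally likely.

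**4. Whom the safeguards protect.** The separate administrator and the request for silence both act between the product and the investigator. The participant swallows the product each time and takes the fourth dose at home (Trial procedures and follow-up). Nothing described masks taste or smell.

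**5. Which endpoints are open to this.**
- Self-reported: SF-8, EQ-5D and BPI (Outcomes), with questionnaires repeated at the final visit.
- Acceptability: named in the secondary objectives.
- Adverse events: the side effects listed under Safety include gastrointestinal symptoms that depend on participant report.
- HbA1c: measured in hospital laboratories whose staff are stated to be blind. An effect could arise only indirectly, through behaviour.
- 25(OH)D: assayed at the end of the trial, so it cannot unblind anyone during follow-up.

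**6. What the block of 6 adds.** Assume an observer who recognises D2, knows the block size and boundaries, and sees every earlier product in that block. With two packs per arm there are 90 possible orders of a block.
- Not-D2 is certain once both D2 packs have gone. Each of the four other packs falls after both with probability 1/3, so 4 × 1/3 = 1.33 of 6 (22.2%).
- D2 is certain at the sixth position if one D2 pack remains (probability 1/3) and at the fifth if two remain (1/15). 1/3 + 1/15 = 0.40 of 6 (6.7%).
- D2 status is known in advance for 1.33 + 0.40 = 1.73 of 6 (28.9%). The exact arm is known for 6.7%. D3 versus placebo is never known.
- Over the 90 orders, expected correct three-arm guesses rise from 2.00 to 2.80 of 6 (33% to 47%).

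If no product is recognised, no allocation becomes certain.

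**The case against.** The strongest reply is that different vehicles do not amount to known allocation. Each participant takes one product and has no comparator. Nothing shown says that participants are told which vehicle belongs to which arm, and the participant information is not available to check. The request for silence concedes that characteristics differ, not that participants identify their arm. This stands: a reader might infer that the D2 arm was in fact unblinded, and the article does not support that.

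A reader might also infer that the administering person's knowledge contradicts the blinding statement. It does not. That statement names participants, investigators and laboratory staff only, and a separate person is used precisely because the products differ.

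A reader might further infer that the fixed block of 6 lets allocations be worked out. Alone it reveals nothing. Prediction needs all the conditions in the working, and the article does not say who at the sites knows the block size or whether the two sites share a list. An outside laboratory packs the products.

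Finally, the consequence is limited. The primary endpoint is a laboratory measure. Secondary endpoints carry no p-values and are to be read cautiously, safety is descriptive, and the Discussion says the study is too small for D2 versus D3. All of this limits the reach, but none of it restores a matched comparator for D2.

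**Conclusion.** The concern holds as a mismatch between the blinding that is stated and the blinding that the formulations can deliver. Participant blinding is secured for D3 versus placebo. It is not secured for D2 versus placebo or for the exploratory D2 versus D3 contrast. Up to 114 of 342 participants, one third, receive the distinguishable product; this is a ceiling that assumes equal allocation and recognition by every D2 participant, not an estimate of unmasking.

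The consequence falls mainly on SF-8, EQ-5D, BPI, acceptability and reported adverse events in the D2 contrasts. The HbA1c comparisons are little exposed. The block size is a minor conditional risk: at worst, D2 status is predictable for 28.9% of allocations, and D3 versus placebo for none.

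**What to change.** - State blinding by role and contrast: investigators and laboratory staff blind for all arms; participant blinding secured for D3 versus placebo only.
- Report self-reported, acceptability and adverse-event results for D2 versus placebo and D2 versus D3 as not securely participant-blind, and do not give them the same standing as the matched D3 results.
- Add one treatment-guess question at the final visit, after the other questionnaires, and report the answers by arm. If the full protocol already includes one, commit to reporting it. This replaces inference about unmasking with data.

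The cost is one extra question, some wording, and a less favourable blinding statement for D2. Recruitment is described as under way, so participants who have already had their final visit would lack the guess, and the number answering should be given. Varying the block size for allocations not yet generated is optional and secondary.

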### Trial procedures and follow-up

As shown in the Figure 1, each participant has a total of 4 visits to the trial centre and one telephone call at 3 months to discuss the appropriateness of taking the final of the four doses of IMP. The initial visit includes informed consent, assessment of eligibility, administration of questionnaires regarding physical activity, diet, sun exposure, functional status, health utility, and a brief pain inventory, randomisation and administration of the first dose of study IMP. Subsequent visits (and the telephone call) are at monthly intervals. Second and third visits are for safety assessment and observation of consumption of the next two doses of the study IMP, while the 4^th^ (last) dose of the IMP is taken at home prompted by a phone call from the trial staff, if prior safety checks are within normal limits. The final follow-up visit is at the end of 4 months, when questionnaires are repeated and a final set of blood samples are collected.

**Figure 1 F1:**
[figure not shown]
Trial visits and procedures for participants.

### Blood collection and assays

The trial team collects baseline blood samples from all participants during the first visit, after informed consent, to assess levels of serum ionised calcium as well as serum 25(OH)D assay, HbA_1c_ and the other secondary endpoints mentioned earlier. During the second and third visits blood samples are collected only for safety analysis (as described under the section on safety) to make a judgement about continuation of the IMP. During the final (fourth) visit all blood samples are repeated, as during the first visit. Assays for safety monitoring (serum ionised calcium) at all visits are performed contemporaneously. For other trial endpoint assays, the HbA_1c_ samples from the first and fourth visit are analysed immediately on fresh samples, while aliquots for all other assays (including 25(OH)D) are stored frozen at -70°C to be measured at the end of the trial. Thus in summary, blood samples for safety are collected at all four visits, while for other endpoints bloods are collected only at the first (baseline) and fourth (final) visit.

HbA_1c_, the trial primary end-point is measured according to IFCC (International Federation of Clinical Chemistry and Laboratory Medicine) standards in both trial centres (Royal London Hospital Biochemistry Laboratory for East London and Addenbrookes Hospital Biochemistry Laboratory for Cambridge). Results are reported in both IFCC and DCCT units. Serum 25(OH)D measurement is performed at Homerton University Hospital NHS trust laboratory (London). This laboratory participates in the DEQAS quality assurance scheme and measures both 25(OH)D_2_ and D_3_ using the LC/MS/MS (liquid chromatography/ mass spectrometry/mass spectrometry) method which is well validated [48]. The other measurements including parathyroid hormone, fructosamine, hsCRP and lipid assays are also carried out at Homerton University Hospital NHS Trust laboratory.

### Sample size

Sample size calculations showed that 207 participants (69 per randomised group) are required to detect a 0.2% difference in mean HbA_1c_ between the placebo and either vitamin D_2_ or vitamin D_3_ groups (power calculation was based on DCCT units) with 90% power and a 5% significance level, assuming a standard deviation of HbA_1c_ of 0.5%. However, given the importance of the secondary endpoint systolic blood pressure (SBP), a further calculation was performed to estimate the sample size that would be needed to detect a 5 mmHg difference in mean SBP between randomised groups, assuming a standard deviation of 16 mmHg. The assumptions for the sample size calculations were based on data from the ProActive trial [49] and the BanglaDip Study (personal communication). This yielded a requirement of 339 participants (113 in each group). Pragmatically, recruiting this larger number of participants will also mean that the study will still be powered for the primary endpoint (HbA_1c_) even if there are losses to follow up. Because 339 is not divisible by 6 (the block size for randomisation), the target number is 342 across the two test sites.

### Statistical analysis plan

The analysis plan is available at http://www.mrc-epid.cam.ac.uk/files/2013/04/VitDtrial_AnalysisPlan_Sep2012.pdf. In brief, the primary analysis of efficacy endpoints uses an Intention-To-Treat (ITT) population, which includes all participants for whom outcome data are available, in the group to which they were randomised, regardless of the treatment actually received. A secondary analysis of efficacy endpoints uses a Per-Protocol (PP) population. This population excludes individuals who did not comply with the protocol (e.g. individuals who did not take all doses of the IMP). The analysis of safety endpoints uses a safety population, which includes all participants in the group based on treatment actually received. Any individual who received at least one dose of either vitamin D_2_ or vitamin D_3_ will be included in the vitamin D_2_ or vitamin D_3_ group.

Baseline characteristics of the study population will be summarised separately within each randomised group. For continuous variables, means and standard deviations will be presented, unless the variable has a highly skewed distribution, in which case, medians, 25^th^ and 75^th^ percentiles will be presented. For categorical variables, the number and percentage of participants within each category will be presented. For each variable (continuous or categorical), the percentage of missing values will be reported. No p-values will be calculated for these tables.

The primary efficacy endpoint, HbA_1c_, will be compared separately between each treatment group and placebo, using analysis of covariance with adjustment for baseline and centre. Where baseline values are missing, the missing indicator method [50] will be used to enable these participants to be included in the analysis. For both vitamin D_2_ vs. placebo and vitamin D_3_ vs. placebo, the difference in mean HbA_1c_, 95% confidence interval and p-value will be reported. An analysis will be performed to check whether adjusting for age and sex (the stratifiers) in the analysis of covariance model has any impact on the estimated treatment effects; if it has no impact, then they will not be included in the model. HbA_1c_ will be analysed and results will be reported in IFCC units (mmol/mol), and to enable those readers who are still using the DCCT% units, we will also provide equivalent results using the DCCT% units, derived using a previously described conversion formula [51].

For each of the secondary efficacy endpoints, differences in means (for continuous endpoints) or proportions (for binary outcomes) between each treatment group and placebo, together with 95% confidence intervals, will be estimated using the same method described for the primary endpoint. Continuous endpoints with skewed distributions will be log transformed prior to analysis, in which case a ratio of geometric means (and confidence intervals) will be reported.

The number and percentage of participants experiencing any of the safety endpoints will be reported separately within each randomised group, without p values. For the primary endpoint, interactions between treatment group and baseline HbA_1c_, and treatment group and baseline vitamin D will be tested by including the appropriate interaction term in the analysis of covariance model. If the p-value for the interaction test is <0.05, the treatment effects and 95% confidence intervals will be estimated within subgroups defined by levels above and below the median value of either HbA_1c_ or vitamin D.

For the primary efficacy endpoint, two p-values will be calculated, one for the comparison of vitamin D_2_ vs placebo and one for the comparison of vitamin D_3_ vs placebo. No adjustment for multiple testing will be performed. An exploratory analysis will be performed in which mean HbA_1c_ will be compared between the vitamin D_2_ group and the vitamin D_3_ group, using the same method described above. An estimate of the difference in mean HbA_1c_ (adjusted for baseline), together with a 95% confidence interval, will be reported. For all other efficacy endpoints, the treatment effects (vitamin D_2_ vs placebo and vitamin D_3_ vs placebo) will be reported together with a 95% confidence interval. No p-values will be calculated. Interpretation of results for secondary endpoints will be cautious and results that are statistically significant in isolation will be interpreted less strongly than sets of results that are mutually supportive, or which are supported by previous research findings.

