## Background

The number of people with diabetes is increasing across the world, with the latest estimates from the International Diabetes Federation predicting a rise from 366 million in 2011 to 552 million in 2030 [1]. The clinical consequences of type 2 diabetes (T2D) including macrovascular and microvascular disease, and related premature mortality [2] make it a condition of major public health importance. As such, the identification of risk factors for T2D, particularly those that might be potentially modifiable, is of great interest.

There is convincing evidence that changes to diet and physical activity can help to prevent or delay the onset of T2D among those at high risk [3-6]. However, intensive lifestyle modification interventions are difficult to sustain and costly to implement. Thus, there is interest in identifying complementary strategies that might help in the prevention of T2D. There is accumulating evidence that vitamin D insufficiency is associated with the risk of developing T2D [7-9]. Whether supplementation of vitamin D can delay or prevent T2D is unknown.

Epidemiological studies have examined the association between dietary vitamin D intake and the risk of diabetes [10,11], but these omitted information on the major non-dietary component of vitamin D from endogenous synthesis through sun exposure. Circulating 25-hydroxyvitamin D (25[OH]D) concentration is the best indicator of vitamin D status as it accounts for both vitamin D intake and endogenous synthesis [12]. More recent epidemiological studies have examined the association between circulating 25(OH)D concentrations and incident diabetes, and the findings have been largely consistent, demonstrating an inverse association. Such findings have been summarised in systematic reviews and meta-analyses [7-9], with the latest one from our group showing a 41% (95% confidence interval 33% to 48%) lower risk for those in the highest versus the lowest quartile of 25(OH)D [7]. Whilst meta-analysis deals with issues of consistency and precision, it does not resolve the problems of confounding and selection bias in observational studies. To address the question of whether observed associations between vitamin D and risk of T2D are causal in nature, there is a need to conduct randomised controlled trials of supplementation.

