## Methods/design

We designed a double-blind, placebo-controlled randomised clinical trial amongst people at risk of developing T2D, across two sites - East London and Cambridge, UK. We are randomly allocating 342 participants to one of three groups, to receive a monthly dose for four months, of 100,000 IU (equivalent to 2.5 mg) of either cholecalciferol (vitamin D_3_) or ergocalciferol (vitamin D_2_) or a monthly dose of placebo (miglyol oil). Each participant is followed-up for a total of 4 months from their first visit. The inclusion and exclusion criteria of the trial are as follows.

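### The ANCOVA has no visit-date term, so for endpoints that follow season (25(OH)D, PTH if seasonal) the reported confidence intervals are too wide; HbA1c is practically unaffected

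*Protocol article*

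**What the plan says.** In the Statistical analysis plan section of the protocol article, HbA1c in each vitamin D group is compared with placebo "using analysis of covariance with adjustment for baseline and centre". Baseline here is the baseline value of the endpoint being analysed. The only further covariates considered are the stratifiers: "An analysis will be performed to check whether adjusting for age and sex (the stratifiers) in the analysis of covariance model has any impact". For the secondary efficacy endpoints, differences "will be estimated using the same method described for the primary endpoint", and they are reported with 95% confidence intervals and no p-values.

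Baseline vitamin D has one stated role in the HbA1c analysis: the interaction between "treatment group and baseline vitamin D will be tested by including the appropriate interaction term in the analysis of covariance model", followed by a median split if the test is significant.

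The Background names "the major non-dietary component of vitamin D from endogenous synthesis through sun exposure" and faults earlier studies for leaving it out. Methods/design says "Each participant is followed-up for a total of 4 months from their first visit", and Blood collection and assays says "for other endpoints bloods are collected only at the first (baseline) and fourth (final) visit". Sun exposure is recorded by questionnaire at the first visit, and questionnaires are repeated at the last. No stated model uses sun exposure, season or visit date, and the recruitment sections set no season for entry.

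**The concern.** Four months is 120 degrees of the annual cycle. A participant who starts in late summer is expected to lose 25(OH)D under placebo, and one who starts in late winter to gain. The baseline reading cannot absorb this, because the seasonal part at month 4 correlates cos(120°) = -0.5 with the seasonal part at baseline. Predictable variation by date therefore goes into the residual.

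What is at stake is the width of the reported intervals for season-driven endpoints. Width matters because the secondary endpoints are to be read from estimates and intervals alone. 25(OH)D is also the evidence that supplementation raised vitamin D status.

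**Working it through.** The documents give no seasonal figure, so there is none of the plan's own to reproduce.

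**Inputs.** From the protocol article: 4 months between samples; 342 participants in three groups, so 342/3 = 114 per group; blocks of 6 within four age-by-sex strata. Assumed: sinusoidal season with amplitude A = 5, 10 or 15 nmol/L; start dates spread evenly over the year; non-seasonal between-person SD 17; measurement SD 8; correlation r of the non-seasonal level over 4 months equal to 1 or 0.7.

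**Step 1. Residual variance of month-4 25(OH)D under placebo, given baseline only.**
- Variance at each visit: V = 17² + 8² + A²/2 = 353 + A²/2.
- Covariance of the two visits: C = 289r + (-0.5)(A²/2) = 289r - A²/4.
- Residual variance = V - C²/V.

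**Step 2. The same with date terms.** Because cos(u + 120°) = -0.5 cos u - 0.866 sin u, a sine and a cosine of the baseline date also remove the season at month 4. The residual variance becomes 353 - (289r)²/353, which is 116.4 for r = 1 and 237.1 for r = 0.7.

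| r | A | V | C | Residual, baseline only | Residual, with date | Reduction |
|---|---|---|---|---|---|---|
| 1 | 5 | 365.5 | 282.75 | 146.8 | 116.4 | 21% |
| 1 | 10 | 403.0 | 264.0 | 230.1 | 116.4 | 49% |
| 1 | 15 | 465.5 | 232.75 | 349.1 | 116.4 | 67% |
| 0.7 | 5 | 365.5 | 196.05 | 260.3 | 237.1 | 9% |
| 0.7 | 10 | 403.0 | 177.3 | 325.0 | 237.1 | 27% |
| 0.7 | 15 | 465.5 | 146.05 | 419.7 | 237.1 | 43.5% |

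**Step 3. Model standard error of a two-group difference**, √(2 × residual variance / 114), assuming the same residual variance in the active groups:
- r = 1: 1.61, 2.01 and 2.48 without date terms, 1.43 with them.
- r = 0.7: 2.14, 2.39 and 2.71 without, 2.04 with.

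**Step 4. Reported against actual precision.** Small blocks filled in order of entry keep the groups similar in start date, so the estimate varies less than the unadjusted model says. In simulated trials with r = 1, the unadjusted estimate had an empirical SE of 1.43, 1.56 and 1.65, against model SEs of 1.61, 2.01 and 2.48. Reported intervals are then too wide by factors of 1.61/1.43 = 1.13, 2.01/1.56 = 1.29 and 2.48/1.65 = 1.50. With date terms, model and empirical SE agree at about 1.43.

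**Step 5. HbA1c.** A simulation of 342 participants used blocks of 6 in four strata, one-year accrual, season at 3% of total variance and an assumed baseline correlation of 0.69. Mean bias was 0.001 percentage points with and without date terms. The empirical SE was 0.0471 without and 0.0470 with them.

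**The case against.** **The article is a summary.** It points to a full analysis plan that is not shown, and that plan may contain a date term. This stands as a caveat. The article nevertheless names the covariates, says which others will be considered, and extends the method to the secondary efficacy endpoints. If the full plan differs, the two should be reconciled.

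**25(OH)D is not a stated continuous endpoint.** The Outcomes section lists it among other endpoints, as proportions in five categories. This also stands: the percentages above apply to a continuous 25(OH)D comparison and do not carry over to the category proportions. PTH is a listed secondary endpoint, but whether it is seasonal is not in the documents, and no gain is computed for it.

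**The upper figures are favourable.** The 21% to 67% range needs non-seasonal levels that do not change over 4 months. That is why the r = 0.7 rows are shown.

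Three stronger readings are tempting, and the documents do not support them:
- A reader might infer that season distorts baseline vitamin D as a covariate in the HbA1c model. The baseline in that model is baseline HbA1c; baseline 25(OH)D enters only the interaction analysis.
- A reader might infer that stratifying on age and sex alone leaves material imbalance in start month. The blocks of 6 largely prevent this, and randomisation keeps the contrasts unbiased.
- A reader might infer that the baseline vitamin D interaction is invalid. If 5% to 30% of baseline 25(OH)D variance is seasonal (assumed), the interaction slope on year-average status shrinks by 5% to 30%, and about 8% to 22% of participants fall on the other side of the median. But measured baseline status is a legitimate prespecified modifier, year-average status is a different quantity, and a simulation showed no power gain from simply removing season from the baseline value.

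**Conclusion.** The point holds as a minor improvement to the analysis wording. Leaving out visit date does not bias any treatment contrast and makes no practical difference to HbA1c. For endpoints that follow season it leaves explainable variance in the residual, and because blocking already balances start date, the main consequence is intervals wider than the true sampling error.

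Under the assumptions above, for continuous month-4 25(OH)D the residual variance falls by 21% to 67% with perfectly stable non-seasonal levels, and by 9% to 43.5% with a correlation of 0.7. The gain in the estimate itself is smaller than the gain in the interval: with stable levels the empirical SE goes from 1.43, 1.56 or 1.65 to about 1.43. Amplitude, SDs, correlation, even accrual over the year and a common seasonal pattern across groups are all assumed, so the direction is firm and the size is not.

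**What to change.** Add one annual sine and one annual cosine term of the baseline visit date to the models for 25(OH)D and PTH, and state this before unblinding. The same terms are optional for HbA1c and SBP. With a fixed 4-month interval, the baseline date serves for both visits.

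For the treatment-by-baseline-vitamin-D interaction, keep the measured baseline value as specified, and report a date-adjusted version as a sensitivity analysis only.

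If the full analysis plan already has a date term, bring the article's covariate list into line with it.

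The cost is two degrees of freedom per model and a sentence of wording. It needs only the date of the baseline visit, and no new data or visits.
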